## Methods/Design

### Overview

A parallel-group randomized triple-blind placebo-controlled clinical trial, designed according to the CONSORT SPIRIT 2013 guidelines (Additional file 1), will be conducted over a period of 1.5 years from June 2016, in Isfahan, Iran. We will include 120 prediabetic adults [individuals with impaired glucose tolerance (IGT) or impaired fasting glucose (IFG)], as determined by the American Diabetes Association (ADA) criteria [21]. The participants will be selected from first-degree family of type 2 diabetic patients. They will be recruited from the outpatient clinic of Isfahan Endocrine and Metabolism Research Center.

Eligibility criteria for the participants are presented in Table 1. A nutritionist will perform the intervention. The participants will be randomized into three equal groups using a blocking stratified sampling method by age and sex to ensure equal numbers within each age and sex strata using a computerized table of random digits. The groups are probiotic, synbiotic (6 grams inulin + probiotic) or placebo (maltodextrin) consumers for 6 months. The appearance and packaging of the three products are identical. Details about the content and preparation process of pruductes will be presented in section 3.2. The inulin dose of 6 g/d as the prebiotic in the synbiotic type was selected based on previous studies [22]. This dose was suggested and tested to be well-tolerated. Participants, laboratory staff, and investigators will be blinded to the allocation of probiotic, synbiotic or placebo, which will be conducted by the study pharmacist (who will then dispense blinded supplements or placebo to the investigators). The subjects will be instructed to dilute the powder in water and to drink it after their main meal to minimize the killing of the probiotic by gastric acid. Due to the dietary-controlled nature of the study, water was selected as the beverage for the delivery of supplements. Individuals will be appropriately blinded in performing outcome measurements and type of supplement. The supplements will be assigned letter A, B or C and are otherwise identical. All of the participants have been counseled to follow an energy-balanced diet and physical activity recommendations 6 months previous to start of the study. They will be advised not to modify their daily dietary and physical activity habits. To ensure that these habits have not been modified during the experiment, the participants will be instructed to record daily food and physical activity diaries, which will be checked monthly during face-to-face visits by a dietitian. Also, the participants will be advised not to modify their medication during the experiment. During these visits, the researchers will check the compliance with the study supplementation and the development of any adverse events. Compliance will be assessed based on returned tablet counts. The project coordinator will assess and manage solicited and spontaneously reported adverse events of trial interventions.

**Table 1 Tab1:** Eligibility criteria for the effects of probiotic or synbiotic supplementation on metabolic syndrome indices

Inclusion criteria:	
Population: men and women 35–75 years old	
Prediabetic [FBG = 100–125 OR 2hBS = 140–199 (via OGTT)]	
Informed consent	
Exclusion criteria:	
Current smokers, suspected or definite history of alcohol or drug abuse history	
Antibiotic use in the past 3 months or during the treatment period	
Using probiotic, prebiotic or symbiotic during the past 3 months	
Noncompliance in consumption of the supplements	
Being pregnant	
Having gastrointestinal diseases, i.e., food allergies, celiac, irritable bowel disease,	
severe liver, kidney, heart, nervous system diseases	
Allergy to studied agents	
Currently taking prescribed nonsteroidal anti-inflammatory drugs, antipsychotics, nicotinic acid	

*FBG* fasting blood glucose, *2hBS* 2-hour blood sugar, *OGTT* oral glucose tolerance test

If a participant will be found to have missed >10% of supplement dose at follow-up, he or she will be excluded from the study. Also, the participants will be excluded from the study if there is any change in medication, they start antibiotics, or modify their lifestyle. The framework of the study has been provided in Fig. 1. Study visits will be scheduled for weeks 1, 2, 3, 5, 7, 9, 12, 14, 16, 18, 20, 24, 48, and 72. A table of the time schedule of enrollment, interventions, assessments, and visits for participants is provided in Table 2, and an overview of the timeline of the study interventions and assessments is provided in Fig. 2.

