### Product standardization and palatability testing

Participants will be supplemented with 6 g/d of either synbiotics comprising a probiotic with an inulin-based prebiotic, probiotics containing the freeze-dried *Lactobacillus acidophilus*, *Bifidobacter bifidum*, *Bifidobacter lactis*, and *Bifidobacter longum* (10^9^ for each) with maltodextrin as filler, or placebo including maltodextrin for 6 months.

The supplements were prepared and packaged in Tak Gen Zist Pharmaceutical Company, Tehran, Iran in sachet form.

All of microbial and purity tests were checked by two independent microbiologists.

Prior to the onset of the trial, the solubility and palatability of supplements (6 g dose) in a cup of water were assessed to determine the optimal well-tolerated mode of delivery of the supplement prescription.

The researchers will be in weekly contact with participants and any concerns or side effects during the intervention period will be addressed. The participants will be excluded from the study if there is any side effect or problem.

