## Data analysis

### Sample size

Calculation of sample size was based on a parallel three-group randomized clinical trial with repeated measurements of main outcomes at three time points. Considering a type one error rate of $$ \upalpha =0.05 $$, and statistical power of 1 − β = 0.80 (^*Z*^
_1 − *β*_ = 0.84) for detecting a standardized effect size of at least Δ = 0.60 in order to have the largest number of participants in a repeated measures design structure based on the following formula, 29 subjects were determined. Compensating for possible attrition, 30% additional samples will be recruited, in which a final 40 subjects in each study group will participate.$$ R=\left[\frac{1+\left( w-1\right)\;\rho}{w}-\frac{v{\rho}^2}{1+\left( v-1\right)\rho}\right];{n_{1\;}}_{repeated}= R\left[\frac{2{\left({z}_{1-\alpha /2}+{z}_{1-\beta}\right)}^2}{\varDelta^2}+\frac{z_{{}_{1-\alpha /2}}^2}{4}\right] $$

In this formula, Δ is the standardized effect size, R will be determined based on number of observations before intervention, v (in our study v = 1), number of observation after intervention, w (in the current study w = 2) and intracluster correlation coefficient ρ, that was considered as ρ = 0.7 [27].

The participant’s adhesion and retention will be managed by the project coordinator who will conduct weekly contact. We anticipate that it will take 12 months to recruit this sample size. All of the outcome data will be collected even for participants who discontinue or deviate from intervention protocols.

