
### Treatment of missing data

Missing data are common in longitudinal studies. Based on patterns and the mechanism of missing data, an appropriate multiple imputation approach will be followed for completing missing data. We will use an intention-to-treat analysis as our primary analytic approach. As an alternative statistical analysis method using linear mixed model ANOVAs or generalized estimating equation (GEE) for longitudinal analysis, we will compare main study outcomes across the treatment groups. Through employing these methods, the possibility for using all available data to construct weighted averages across the different patterns of missing data to provide valid point estimates, and confidence intervals for population parameters will be provided [28]. As a secondary analysis, we will conduct a per protocol analysis and restrict the analyses to only those individuals who complete the intervention; if the results differ we will interpret the findings based on the intention-to-treat analysis.

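### Randomised participants are excluded from the study for post-randomisation events, which contradicts the promised full follow-up and the intention-to-treat primary analysis

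*Protocol article*

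**What the plan says.** Three sets of statements in the protocol article bear on the same participants.

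**Exclusion after randomisation.** Below Table 1, the Overview states: "If a participant will be found to have missed >10% of supplement dose at follow-up, he or she will be excluded from the study". It continues that "the participants will be excluded from the study if there is any change in medication, they start antibiotics, or modify their lifestyle". The section on product standardization and palatability testing adds: "The participants will be excluded from the study if there is any side effect or problem". Table 1 lists two of these events among its exclusion criteria: "Noncompliance in consumption of the supplements" and "Antibiotic use in the past 3 months or during the treatment period". Noncompliance, and antibiotic use during treatment, cannot be known when a participant is randomised.

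**Follow-up.** The Sample size section promises: "All of the outcome data will be collected even for participants who discontinue or deviate from intervention protocols".

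**Analysis.** Treatment of missing data states: "We will use an intention-to-treat analysis as our primary analytic approach". A per-protocol analysis of those who complete the intervention is secondary, and intention-to-treat decides the interpretation if the two differ.

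On how adherence is measured, the Overview says: "Compliance will be assessed based on returned tablet counts". The same section describes a powder diluted in water, and the product section describes sachets.

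**The concern.** Every ground for exclusion arises after allocation, and each can depend on the product or on the course of the disease. The clearest case is medication. The primary outcome is insulin resistance (HOMA-IR), and a participant whose glucose worsens may start a drug. Under the Overview that participant leaves the study, although the result is informative about the treatment. Adherence and side effects can also depend on what is in the sachet, and the three products differ in content.

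The medication rule has no stated end. Table 2 asks participants not to change medication while in the study, and visits run to week 72, about a year after supplementation ends. The rule could therefore remove participants throughout follow-up.

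At stake is who is in the primary comparison. If deviators leave, the intention-to-treat set holds little or no later data on them, and the per-protocol analysis is no longer an independent check on it. Data not collected at a visit cannot be recovered.

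**Working it through.** **1. The passages side by side**

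| Event | Overview, Table 1 and product section | Sample size section | Treatment of missing data |
|---|---|---|---|
| More than 10% of doses missed | excluded from the study | data still collected | analysed as randomised |
| Medication change, antibiotics, lifestyle change | excluded from the study | data still collected, if a deviation | analysed as randomised |
| Any side effect or problem | excluded from the study | data still collected, if supplement is discontinued | analysed as randomised |

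The first column agrees with the other two only if exclusion means coming off the supplement or out of the per-protocol set. No section says so.

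**2. Is the harm loss of power or bias?**

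The plan gives no figure for exclusions by arm, only a 30% attrition allowance and 40 per group. With its stated inputs (Δ = 0.60, v = 1, w = 2, ρ = 0.7), R = (1 + 0.7)/2 - 0.49 = 0.36. Approximate power is Φ(Δ/√(2R/n) - 1.96). This gives 0.994 at n = 40, and 0.963 at n = 40 × 0.7 = 28. On the plan's own inputs, loss of numbers is not the problem. Bias is.

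**3. Illustration A: true benefit, exclusion for a poor outcome (assumed mechanism)**

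Take placebo as N(0, 1) and active as N(-0.60, 1), where lower is better. Everyone above a cut c is excluded. The mean of those left is μ - φ(c - μ)/Φ(c - μ). For c = z(0.85) = 1.036:

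- Placebo: -0.2332/0.85 = -0.274.
- Active: -0.60 - 0.1046/0.9491 = -0.710, with 5.1% removed.
- Difference: -0.710 + 0.274 = -0.436. The shrinkage is 1 - 0.436/0.60 = 27%.

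| Placebo removed | Active removed | Difference among those left | Shrinkage |
|---|---|---|---|
| 10% | 3.0% | -0.475 | 21% |
| 15% | 5.1% | -0.436 | 27% |
| 20% | 7.5% | -0.403 | 33% |

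This is an upper-end case, because the cut acts on the outcome itself. If the trigger is a separate variable, also shifted by 0.60 SD and correlated r with the outcome, the difference is -0.60 + r × (0.60 - 0.436). At 15% of placebo removed this gives -0.55, -0.52 and -0.49 for r = 0.3, 0.5 and 0.7, a shrinkage of 8% to 19%.

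**4. Illustration B: no true effect, more exclusions on active (assumed mechanism)**

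Suppose excluded participants are worse than their arm mean by k SD. An arm that loses a share e then has a retained mean of -k × e/(1 - e). With e = 30% on active and 10% on placebo, the bias is -k × (0.4286 - 0.1111) = -0.317k. The standard error with R = 0.36 is √(0.36 × (1/28 + 1/36)) = 0.151.

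| k | Bias (SD), 30% vs 10% | Type I error | Bias (SD), 20% vs 10% | Type I error |
|---|---|---|---|---|
| 0.3 | -0.10 | 10% | -0.04 | 6% |
| 0.5 | -0.16 | 18% | -0.07 | 8% |
| 0.8 | -0.25 | 39% | -0.11 | 12% |

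With equal exclusion and equal selection in both arms, the bias is 0.

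Illustration A works against the supplements and illustration B works in their favour. The documents do not show which mechanism would dominate.

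**The case against.** The strongest reply is that the article already addresses these participants. It promises their outcome data, makes intention-to-treat primary and lets it govern. If exclusion is read as removal from the intervention, the statements fit together and no bias of this kind arises. That reading is possible, so a reader should not infer that the planned primary analysis is simply a completer analysis. But the reading is not written down. The exclusion sentences name the study, not the supplement, and site staff could follow them literally.

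Four stronger readings are tempting, and the documents do not support them:

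- **That loss will differ by arm, or that the bias has a known direction.** The Overview says the inulin dose was tested as well tolerated. No exclusion rates by arm are given, and the two illustrations point opposite ways.
- **That 27% is the expected bias.** It assumes a deterministic cut on the outcome, and no HOMA-IR threshold for starting medication is stated. Truncation also narrows the spread (pooled SD about 0.85), so the standardised difference is -0.436/0.85 = -0.51, about 15% short of -0.60. The calculation also ignores baseline adjustment and use of month-3 data.
- **That the plan relies on missing-at-random imputation.** It says the approach will follow the pattern and mechanism of missingness. What stands is that standard imputation cannot be relied on when exclusion depends on outcomes that were never recorded.
- **That harms are under-counted.** Adverse events are recorded at the scheduled contacts, so the side effect that triggers exclusion would itself be recorded. At most, later events are lost.

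The tablet wording is a separate slip and adds nothing to the severity.

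**Conclusion.** The contradiction is real and needs to be resolved: the exclusion rules and the two Table 1 criteria conflict with the follow-up promise and the intention-to-treat primary analysis. The bias is conditional. It arises if the exclusions are applied as written and exclusion depends on both arm and outcome, and it does not arise if the Sample size and Treatment of missing data sections govern. Its direction cannot be known in advance.

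On assumed mechanisms, a true -0.60 SD could shrink to between -0.48 and -0.40 at the upper end, with less under weaker selection. In the other direction, a null effect could appear as a benefit of 0.04 to 0.25 SD. These figures show why the ambiguity matters. They do not predict what this trial will show.

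**What to change.** Reconcile the Overview, Table 1, the product section, the Sample size section and Treatment of missing data so that they state one rule:

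1. Record missed doses, medication change, antibiotics, lifestyle change and side effects as protocol deviations or supplement discontinuation, with date and reason.
2. Keep every randomised participant in the scheduled assessments to week 72 and in the primary intention-to-treat analysis.
3. Use these events only to define the secondary per-protocol set. Align that set's present definition, completion of the intervention, with them.
4. Take both post-randomisation items out of the Table 1 eligibility criteria: noncompliance, and the part of the antibiotic criterion that refers to the treatment period.
5. State separately whether supplement is stopped after a side effect or another such event. That is a clinical decision, distinct from remaining in follow-up, and this review takes no position on it.
6. Minor: align the compliance measure with the product, which is powder in sachets.

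The cost is protocol wording. The follow-up visits for participants who discontinue or deviate are already promised in the Sample size section.

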**Fig. 1 Fig1:**
[figure not shown]
Study design schematic

**Table 2 Tab2:** Time schedule of enrollment, interventions, assessments, and visits for participants

Week	Visits and activities
Prior to starting the study	Patients who meet eligibility criteria will be asked to read and sign the consent form
Week 1	Patients will be instructed on writing the food and physical activity records and procedures for collection of stool samples. They will be asked not to take any other dietary supplementation or probiotics and not to change their medication and/or lifestyle while in the study and to inform the researchers if they are prescribed oral antibiotics at any time during the study
Week 2	Stool samples, food record and physical activity record will be collected. Weight, height, waist and hip circumferences, and blood pressure will be measured. Biochemical tests will be performed. The supplement will be delivered
Week 3, 5, 7, 9	Contact with the participants and effectiveness or adverse event will be recorded.
Week 12	Food record and physical activity record will be collected. Weight, height, waist and hip circumferences, and blood pressure will be measured. Biochemical tests will be performed. The supplement will be delivered
Week 14, 16, 18, 20	Contact with the participants and effectiveness/adverse event will be recorded
Week 24	Stool samples, food record and physical activity record will be collected. Weight, height, waist and hip circumferences, and blood pressure will be measured. Biochemical tests will be performed
Week 48, 72	Food record and physical activity record will be collected. Weight, height, waist and hip circumferences, and blood pressure will be measured. Biochemical tests will be performed

**Fig. 2 Fig2:**
[figure not shown]
Template of content for the schedule of enrollment, interventions, and assessments

### Product standardization and palatability testing

Participants will be supplemented with 6 g/d of either synbiotics comprising a probiotic with an inulin-based prebiotic, probiotics containing the freeze-dried *Lactobacillus acidophilus*, *Bifidobacter bifidum*, *Bifidobacter lactis*, and *Bifidobacter longum* (10^9^ for each) with maltodextrin as filler, or placebo including maltodextrin for 6 months.

The supplements were prepared and packaged in Tak Gen Zist Pharmaceutical Company, Tehran, Iran in sachet form.

All of microbial and purity tests were checked by two independent microbiologists.

Prior to the onset of the trial, the solubility and palatability of supplements (6 g dose) in a cup of water were assessed to determine the optimal well-tolerated mode of delivery of the supplement prescription.

The researchers will be in weekly contact with participants and any concerns or side effects during the intervention period will be addressed. The participants will be excluded from the study if there is any side effect or problem.

### Biochemical assays

Participants who have met the inclusion criteria (Table 1) will be instructed to arrive at Isfahan Endocrine and Metabolism Research Center for laboratory testing between 7:00 and 9:00 am after a 12-hour overnight fast and not to do vigorous physical activity for the previous 48 hours. Each participant will be tested for the biochemical parameters at baseline and during each follow-up visit (3, 6, 12, and 18 months).

An oral glucose tolerance test (OGTT) will be performed to clarify glycemic status. Plasma lipid and lipoprotein concentrations (i.e., total cholesterol, high- and low-density lipoprotein cholesterol, and triglycerides) will be measured using a photometric assay kit (Pars Azmoon Co., Tehran, Iran). Fasting glucose levels will be measured using the glucose oxidase (GOD) method. Fasting insulin levels will be measured using chemiluminescence (Siemens, Munich, Germany). Ion exchange chromatography will be used to test glycosylated hemoglobin (HbA1c).

The homeostatic model assessment of insulin resistance (HOMA-IR) and homeostatic model assessment of beta-cell function (HOMA-B) index will be used to determine insulin resistance (primary outcome) and beta-cell function respectively using the following formula:$$ \mathrm{HOMA}\hbox{-} \mathrm{I}\mathrm{R}=\mathrm{fasting}\;\mathrm{blood}\;\mathrm{glucose}\;\left(\mathrm{mmol}/\mathrm{ml}\right)\times \mathrm{insulin}\;\mathrm{assay}\;\left(\mathrm{microunit}/\mathrm{ml}\right)/22.5 $$
$$ \upbeta \kern0.5em \mathrm{cell}\kern0.5em \mathrm{function}\kern0.5em \left(\mathrm{HOMA}\hbox{-} \mathrm{B}\right)=\left[\mathrm{fasting}\ \mathrm{insulin} \times 20\right]/\left[\mathrm{fasting}\ \mathrm{glucose}\hbox{-} 3.5\right] $$

### Anthropometric parameters and blood pressure measurement

Height, weight, waist and hip circumferences will be measured at baseline and will be repeated at months 3, 6, 12, and 18.

Height will be determined using a scale-mounted stadiometer to the nearest 0.5 cm and weight will be measured with light clothing to the nearest 0.1 kg. BMI will be calculated by dividing each participant’s weight in kilograms by height in meters squared. Waist circumference will be measured at the midpoint between the lowest rib and the iliac crest to the nearest 0.1 cm using a flexible tape. Hip circumference will be measured around the widest portion of the buttocks by the tape. The waist-to-hip ratio (WHR) will be calculated according to World Health Organization (WHO) recommendations [23]. All the measurements will be taken by one person to decrease the error rate.

Blood pressure for each participant will be measured by a trained nurse on two occasions using a mercury sphygmomanometer in both of the hands and the mean blood pressure readings will be used for the analysis according to American Heart Association guidelines [24]. Participants will be instructed to rest for 10 minutes prior to the first blood pressure measurement with a minimum of 15 minutes between the two occasions.

### Assessment of physical activity and dietary intake

Food and physical activity records will be assessed at five time points during the study (at months 0, 3, 6, 12, and 18). At each time point, participants will be instructed to record their daily food and beverage intake for 3 days, including a weekend day. To enhance portion size accuracy, food scales and models will be also used. The portion sizes will be converted to grams, and every food and beverage item will be subsequently coded and analyzed for energy content, macro and micro nutrients using Nutritionist 4 [25].

Physical activity will be assessed using the metabolic equivalent of task (MET) questionnaire [26].

